### DLT

We pre-defined the DLT before the start of the study, which included any of the following adverse events during the procedure:

Symptomatic intracranial hemorrhage within 36 h after IVT (25).Parenchymal hemorrhage type 2 within 36 h after IVT (26).Major bleeding and clinically relevant non-major bleeding within 36 h after IVT (27, 28).

### Outcomes

The primary endpoint is the determination of the MTD based on DLTs. Secondary outcomes will be evaluated as follows: mRS score at 90 days; the proportion of patients achieving favorable functional outcomes, defined as an mRS score of 0–1, at 90 days; the proportion of patients exhibiting substantial neurological improvement on the NIHSS, defined as a decrease of at least 4 points, a score no more than 1, at 7 days or at discharge; fibrinogen level at 6 h post-treatment; symptomatic intracranial hemorrhage within 90 days, as defined by the European Cooperative Acute Stroke Study III (25); parenchymal hemorrhage type 2 within 90 days, as defined by the Safe Implementation of Thrombolysis in Stroke-Monitoring study (26); any intracranial hemorrhage within 90 days; major or clinically relevant non-major bleeding within 90 days (27, 28); BI score at 90 days; all-cause mortality within 90 days. Both serious and non-serious adverse events will be collected up to 90 days.

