## Methods and analysis

This study is a prospective, single-center, open-label, phase I, single-arm, dose-escalation clinical trial. A rolling-six design (16–19), a rule-based phase I dose-escalation method that allows concurrent enrollment of 2 to 6 participants at a given dose level, will be used (16). This design was selected because it reduces delays associated with sequential enrollment and can provide more safety information than the conventional 3 + 3 approach (16, 20). The study design is illustrated in Figure 1. The primary objective is to determine the MTD of urokinase thrombolysis in patients with AIS and to develop an optimal weight-based dosing regimen. This study has been approved by the Ethics Committee of Xuanwu Hospital and registered with Clinicaltrials.gov (Identifier: NCT07047326). All participants will provide written informed consent prior to enrollment in the study.

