### Procedures

Eligible patients will be screened consecutively and enrolled at Xuanwu Hospital according to the predefined inclusion and exclusion criteria. Upon enrollment, patients will undergo baseline assessments, including electrocardiography, complete blood count, routine serum biochemistry (including liver function, renal function, electrolytes, and blood glucose), and coagulation studies (including prothrombin time, international normalized ratio, activated partial thromboplastin time, fibrinogen, and thrombin time). After informed consent is obtained, a baseline NIHSS examination will be performed (21), and patients will be treated with urokinase at the pre-specified dose calculated for their estimated body weight. In this study, the planned dose levels are 15,000 IU/kg, 20,000 IU/kg, 25,000 IU/kg and 30,000 IU/kg. No patient in any dosage tier will receive more than that dose calculated for a 100 kg person. These dose levels were selected based on the currently recommended empirical dosing range for intravenous urokinase and recent observational dose-exploration data. Dose escalation will proceed according to the following steps.

Firstly, 2 to 6 patients will be enrolled concurrently at the 15,000 IU/kg dose level. (a) If none of the evaluable patients at the current dose level experiences a dose-limiting toxicity (DLT, which is defined below), the dose will be escalated to 20,000 IU/kg. (b) If data for one or more enrolled participants is unavailable, or if one patient develops a DLT at 15,000 IU/kg, the new participant will enter at the same dose level. If one of the first 6 participants experiences a DLT, up to 6 additional participants (for a total of 12) will be enrolled at the same dose level to further assess safety and tolerability. If no more than 2 out of 12 patients experience DLTs, the dose will be escalated to 20,000 IU/kg. If exactly 3 out of 12 patients experience DLTs, the 15,000 IU/kg dose level will be considered the MTD. If more than 3 out of 12 patients develop DLTs, the previous dose (if applicable) will be defined as the MTD, and dose escalation will be halted. (c) If 2 patients experience DLTs at the current dose level before expansion, dose escalation will be terminated, and the previous dose level will be determined as the MTD.

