The exact time of treatment initiation will be documented. Urokinase will be diluted in 100 mL of normal saline and administered via intravenous infusion over 30 min. Upon completion of thrombolysis, patients will be admitted to either the stroke unit or the neuro-intensive care unit and will subsequently receive secondary preventive therapy in accordance with established clinical guidelines (7). Fibrinogen levels will be measured at baseline and at 6 h post-treatment. Non-contrast computed tomography or magnetic resonance imaging will be performed within 36 h after treatment to detect hemorrhage, with additional imaging conducted in cases of clinical deterioration or at the discretion of the treating physicians. All imaging data will be independently reviewed for intracranial hemorrhage by two experienced physicians blinded to patient information. Discrepancies between reviewers will first be resolved by consensus; if disagreement persists, a third senior physician blinded to patient information will adjudicate the case. The final adjudicated result will be used for hemorrhage classification and related safety analyses. Neurological assessments using the NIHSS will be performed at baseline, 24 h, 36 h, and at 7 days or discharge after stroke onset. The Barthel Index (BI) and mRS will be assessed at 7 days or at discharge, and again at 3 months (22, 23). Ischemic stroke subtype will be classified according to the Trial of Org 10,172 in Acute Stroke Treatment criteria at 7 days or discharge, based on all available clinical diagnostic data (24). The mRS score at 90 days will be assessed either in person or via telephone interview. The schedule of enrolment, treatment, and follow-up assessments is summarized in Table 1.

**Table 1 tab1:** Schedule of enrolment, treatment, and outcome assessments in the OUTSET study.

Assessments	Screening/baseline	During urokinase infusion (0–30 min)	6 h post-treatment	24 h	36 h	Day 7 or at discharge	Day 90 (±7 days)
Eligibility assessment (inclusion/exclusion criteria)	×						
Written informed consent	×						
Demographic data	×						
Medical history and vascular risk factors	×						
Previous medication	×						
Physical examination and vital signs	×	×	×	×	×	×	
NIHSS	×			×	×	×	
Pre-stroke mRS	×						
Complete blood count	×						
Serum biochemistry	×						
Coagulation studies	×						
Fibrinogen	×		×				
Brain CT or MRI	×				×		
Urokinase administration		×					
Documentation of treatment start time		×					

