### Sample size

The sample size was determined by the rolling-six dose-escalation design rather than by a conventional efficacy-based power calculation. Under this design, 2 to 6 participants may be enrolled concurrently at each dose level, and dose-escalation decisions are based on the number of participants currently enrolled and evaluable, the number who experience DLTs, and the number who remain under DLT observation (16). Therefore, 6 participants represent the maximum initial evaluable cohort size for dose-escalation decisions at a given dose level, rather than the total number considered sufficient for the entire study (16, 20). Published applications of the rolling-six framework have shown that the total number enrolled at a given dose level may exceed 6 because non-evaluable participants can be replaced and additional patients may be enrolled to further characterize safety after a dose level has been judged acceptable (19, 20). In our protocol, participants who are not evaluable for dose-escalation decisions will be replaced according to the prespecified rolling-six rules, and if one DLT occurs among the first 6 evaluable participants at a dose level, that cohort may be expanded to 12 participants for further safety evaluation. With four planned dose levels, the expected total sample size ranges from 24 to 48 participants, depending on the occurrence of DLTs and cohort expansion.

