### Statistical analysis

Given that this study employs a rolling-six design for dose escalation to identify an optimal weight-adjusted dosing regimen, the results will be summarized descriptively. Continuous variables will be presented as means (±standard deviation, SD) or medians (interquartile range, IQR), as appropriate, and compared using either the Student’s *t*-test or the Mann–Whitney *U* test. Categorical variables will be summarized as frequencies and percentages and compared using the Chi-square test or Fisher’s exact test. A two-sided significance level of 0.05 will be applied to all analyses. Statistical analyses will be performed using SPSS Statistics version 26 (IBM Corp., Armonk, NY, United States). All participants who receive urokinase will be included in the safety analysis. Reasons for withdrawal, dropout, or non-evaluable status will be recorded. Participants who are not evaluable for dose-escalation decisions will be handled according to the prespecified rolling-six rules.

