The rolling-six dose-escalation design allows cautious stepwise escalation guided by real-time safety data, with predefined DLT criteria to ensure participant safety. Continuous monitoring by an independent DSMB will further mitigate risk. We retained NIHSS ≥1 in the eligibility criteria because a low NIHSS score does not necessarily indicate a non-disabling stroke, and some patients with low scores may still have clinically meaningful deficits warranting intravenous thrombolysis. To reduce heterogeneity, however, enrollment was limited to patients with clinically disabling symptoms or those otherwise judged appropriate for intravenous thrombolysis, while patients with isolated mild, non-disabling deficits were excluded. Patients with planned or prior endovascular therapy were excluded to minimize confounding from mechanical reperfusion and to allow a clearer assessment of the dose–toxicity relationship of intravenous urokinase itself in this phase I setting (32, 33). Accordingly, the MTD identified in the present study should be interpreted as a foundational safety dose for patients treated without EVT, rather than as a dose directly generalizable to all patients with large-vessel occlusion. Future phase II/III studies should therefore evaluate the applicability of this dose in LVO populations separately, ideally through prespecified stratification, or, more preferably, a dedicated safety lead-in cohort in patients undergoing EVT. The study further incorporated an analysis of serum fibrinogen levels, aiming to offer an additional perspective for evaluating the risk of post-thrombolysis bleeding complications (34). By determining the MTD and characterizing the safety profile of weight-based urokinase thrombolysis, the OUTSET study will establish a scientific foundation for the next generation of clinical trials. The resulting evidence could support the development of standardized and affordable thrombolytic protocols, particularly in settings where urokinase remains a clinically relevant treatment option.

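### Fibrinogen is planned at baseline and 6 h in every patient, but the outcome is the 6 h level alone and the only stated tests ignore baseline, which costs precision in small sequential dose cohorts

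*Protocol article*

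**What the plan says.** Under Outcomes, the protocol article lists "fibrinogen level at 6 h post-treatment" among ten secondary outcomes. It mentions neither change from baseline nor a baseline covariate.

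The baseline value is planned. Procedures states "Fibrinogen levels will be measured at baseline and at 6 h post-treatment", the enrolment work-up contains "coagulation studies (including prothrombin time, international normalized ratio, activated partial thromboplastin time, fibrinogen, and thrombin time", and the fibrinogen row of Table 1 marks the same two times.

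Statistical analysis first says that results are summarised descriptively. It then says "Continuous variables will be presented as means" or medians, compared by t-test or Mann–Whitney test, with two-sided 0.05 applied to every analysis. No adjusted model appears.

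Methods and analysis describes a "prospective, single-center, open-label, phase I, single-arm, dose-escalation clinical trial". Under Sample size, "2 to 6 participants may be enrolled concurrently at each dose level", and after one dose-limiting toxicity "that cohort may be expanded to 12 participants for further safety evaluation".

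The Discussion gives the purpose of the fibrinogen analysis as "aiming to offer an additional perspective for evaluating the risk of post-thrombolysis bleeding complications".

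**The concern.** The trial collects a paired measurement, and the stated outcome and tests use half of it. Patients with low fibrinogen before treatment will tend to have low fibrinogen at 6 h whatever the dose. In cohorts this small, baseline means will differ between levels, and some of that difference reappears in the 6 h comparison.

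The stake is how readable the fibrinogen result is. Fibrinogen is the only laboratory marker that Table 1 schedules after treatment, and so the only one that could show a graded drug effect across doses. The same outcome list judges neurological improvement against the patient's own baseline NIHSS; fibrinogen is not treated that way.

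**Working it through.** **Inputs from the article.** Four dose levels; an initial cohort of up to 6 and an expanded cohort of 12 per level; sequential, non-randomised allocation; fibrinogen at baseline and 6 h; unadjusted two-group tests.

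**Inputs that are assumptions.** The article gives no fibrinogen SD and no baseline-to-6 h correlation r. Results are therefore in SD units, with equal SDs at the two times, and r is varied.

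**The plan's own figure.** 4 × 6 = 24 and 4 × 12 = 48, which reproduces the stated range of 24 to 48 participants. No figure is stated for fibrinogen.

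**Step 1: chance gap in baseline means between two levels.** Its SD is √(2/n).
- n = 6: √(2/6) = 0.58 SD; a gap above 0.5 SD has probability 39%, above 1 SD 8%.
- n = 12: √(2/12) = 0.41 SD; the probabilities are 22% and 1.4%.

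**Step 2: share carried into the 6 h level.** A baseline gap d contributes r × d. Over chance gaps, the carried part has SD r√(2/n): 0.29 to 0.46 SD at n = 6 and 0.20 to 0.33 SD at n = 12, for r from 0.5 to 0.8.

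**Step 3: variance relative to the raw 6 h level.**

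| r | Raw 6 h level | Change score, 2(1 − r) | Baseline-adjusted, 1 − r² |
|---|---|---|---|
| 0.3 | 1 | 1.40 | 0.91 |
| 0.5 | 1 | 1.00 | 0.75 |
| 0.7 | 1 | 0.60 | 0.51 |
| 0.8 | 1 | 0.40 | 0.36 |

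The adjusted column assumes that the slope on baseline is known. Estimating it in a two-level comparison multiplies the variance of the dose difference by about 1 + 1/(2n − 4).
- n = 6: 1 + 1/8 = 1.125, giving 0.84, 0.57 and 0.41 at r = 0.5, 0.7 and 0.8. At r = 0.3 it is 0.91 × 1.125 = 1.02, so there is no gain.
- n = 12: 1 + 1/20 = 1.05, giving 0.79, 0.54 and 0.38.

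**Step 4: power for a true difference of 1 SD, two-sided 0.05.** A normal approximation with known slope gives 41% raw against 52%, 68% and 82% adjusted (r = 0.5, 0.7, 0.8) at n = 6, and 69% against 81%, 93% and 98% at n = 12. These are optimistic for such small groups. A simulation with t-tests and an estimated slope (40,000 runs per setting) gives 35% raw against 40%, 54% and 69% at n = 6, and 65% against 75%, 89% and 97% at n = 12. The direction is the same and the gain is smaller.

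**Step 5: a systematic baseline shift.** Chance gaps are already in the standard error of the unadjusted test, so they do not raise its error rate. A systematic shift would. With an assumed shift of 0.5 SD and no drug effect, the nominal 5% t-test on the raw level is positive in 6.7% (r = 0.5) to 9.9% (r = 0.8) of runs at n = 6, and in 9.3% to 15.6% at n = 12 (20,000 runs). The 0.5 SD is hypothetical.

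**The case against.** The other side has a fair case. Naming a level and a time says what is measured; whether baseline enters a model is often left to an analysis plan, which is not shown here. The Discussion speaks of fibrinogen levels, and the absolute level at 6 h bears on bleeding risk in its own right. No section names a fibrinogen test between doses, and the analysis is introduced as descriptive. The outcome is one of ten secondary outcomes and enters no escalation decision.

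Much of this stands. It rules out replacing the 6 h level with a change score, which would drop the quantity that the Discussion names and would be less variable than the raw level only if r exceeds 0.5. It also limits the point to any comparison across levels that is actually made.

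A reader might infer that the raw outcome invents dose trends. The article does not support that. Chance imbalance adds noise, not false positives, and bias needs a systematic difference between successive cohorts. The article shows none: there is one centre, one set of criteria and consecutive screening. A reader might also infer that the trial sets out to isolate the fall in fibrinogen caused by urokinase; the stated purpose does not go that far.

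What the objection does not remove is that the article does state a method for continuous variables, that this method is unadjusted, and that a better one is available from data already planned.

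**Conclusion.** The point holds as a minor improvement to an exploratory secondary outcome. Any comparison of the 6 h level across dose levels by the stated tests would be less precise than it need be. The residual variance with adjustment is 0.75, 0.51 or 0.36 of the raw value at r = 0.5, 0.7 or 0.8; after paying for an estimated slope at 6 per level the figures are 0.84, 0.57 and 0.41. If r is near 0.3, nothing is gained at that cohort size. Bias is conditional on a systematic baseline difference between cohorts, which sequential filling permits but the article does not show.

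The sizes rest on assumed correlations, equal SDs and a common linear slope. That fibrinogen will be compared across doses is inferred from the general sentence on tests and the aim of describing dose and toxicity. Dose-limiting toxicity counts, escalation and the maximum tolerated dose are unaffected.

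**What to change.** In Outcomes, keep the 6 h level as the outcome. Add absolute and percent change from baseline to 6 h as descriptive summaries, with each patient's baseline and 6 h values shown by dose level.

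In Statistical analysis, add that any comparison of fibrinogen across dose levels will use a linear model of the 6 h value (log scale if skewed) on dose level plus baseline fibrinogen, reported with a 95% CI, provided that at least two levels are enrolled. One model over all enrolled levels is preferable to a series of pairwise tests, because the baseline slope is then estimated from all patients.

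The cost is a sentence or two in each section, one extra model term, and the loss from the model of any patient without a baseline value, which the schedule already requires. No new patient, visit or blood sample is needed. Adjustment deals with baseline fibrinogen only, so other differences between successive cohorts remain a limitation to state when reporting.

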### Safety monitoring

An independent Data and Safety Monitoring Board (DSMB), composed of a neurologist, a neuroradiologist, and a methodologist who have no professional or financial relationship with the study investigators, is responsible for overseeing trial safety and progress. The DSMB reviews and evaluates all DLTs and adverse events on the basis of clinical symptoms, laboratory tests, and imaging data, providing independent recommendations to the investigators on whether the trial should be continued, modified, or terminated.

### Sample size

The sample size was determined by the rolling-six dose-escalation design rather than by a conventional efficacy-based power calculation. Under this design, 2 to 6 participants may be enrolled concurrently at each dose level, and dose-escalation decisions are based on the number of participants currently enrolled and evaluable, the number who experience DLTs, and the number who remain under DLT observation (16). Therefore, 6 participants represent the maximum initial evaluable cohort size for dose-escalation decisions at a given dose level, rather than the total number considered sufficient for the entire study (16, 20). Published applications of the rolling-six framework have shown that the total number enrolled at a given dose level may exceed 6 because non-evaluable participants can be replaced and additional patients may be enrolled to further characterize safety after a dose level has been judged acceptable (19, 20). In our protocol, participants who are not evaluable for dose-escalation decisions will be replaced according to the prespecified rolling-six rules, and if one DLT occurs among the first 6 evaluable participants at a dose level, that cohort may be expanded to 12 participants for further safety evaluation. With four planned dose levels, the expected total sample size ranges from 24 to 48 participants, depending on the occurrence of DLTs and cohort expansion.

### Statistical analysis

Given that this study employs a rolling-six design for dose escalation to identify an optimal weight-adjusted dosing regimen, the results will be summarized descriptively. Continuous variables will be presented as means (±standard deviation, SD) or medians (interquartile range, IQR), as appropriate, and compared using either the Student’s *t*-test or the Mann–Whitney *U* test. Categorical variables will be summarized as frequencies and percentages and compared using the Chi-square test or Fisher’s exact test. A two-sided significance level of 0.05 will be applied to all analyses. Statistical analyses will be performed using SPSS Statistics version 26 (IBM Corp., Armonk, NY, United States). All participants who receive urokinase will be included in the safety analysis. Reasons for withdrawal, dropout, or non-evaluable status will be recorded. Participants who are not evaluable for dose-escalation decisions will be handled according to the prespecified rolling-six rules.

## Discussion

Although urokinase has been widely used for thrombolysis in AIS for several decades in China, its optimal dosing strategy remains inadequately defined (13, 29–31). The currently recommended fixed-dose range of 1.0–1.5 million IU fails to account for individual variability in body weight and pharmacokinetics, leading to heterogeneous efficacy and safety outcomes in real-world practice, such variability may result in suboptimal treatment, including insufficient dosing that limits thrombolytic efficacy or excessive dosing that increases hemorrhagic risk. Establishing a scientifically grounded, weight-based dosing regimen is therefore essential to maximize thrombolytic benefit while minimizing the risk of ICH.

The study is designed to identify the MTD of urokinase in patients with AIS. The selected dose range of 15,000–30,000 IU/kg was based on current empirical clinical dosing practice and supported by recent observational dose-exploration findings suggesting that higher weight-adjusted doses (approximately 23,000–30,000 IU/kg) may be associated with better functional outcomes without an apparent increase in symptomatic intracranial hemorrhage (15). Accordingly, 15,000 IU/kg was selected as a conservative starting dose and 30,000 IU/kg as the upper boundary for dose escalation. The intermediate dose levels of 20,000 IU/kg and 25,000 IU/kg, using 5,000 IU/kg increments, were chosen to allow stepwise safety evaluation across the clinically relevant range while avoiding excessive dose gaps between adjacent cohorts. A prespecified cap at the dose calculated for a 100 kg person was further applied as an additional safety measure. Since observational evidence alone is insufficient to establish an optimized dosing strategy, this prospective dose-escalation study is needed to define the dose–toxicity relationship and identify the MTD, thereby informing subsequent phase II/III trials.

The rolling-six dose-escalation design allows cautious stepwise escalation guided by real-time safety data, with predefined DLT criteria to ensure participant safety. Continuous monitoring by an independent DSMB will further mitigate risk. We retained NIHSS ≥1 in the eligibility criteria because a low NIHSS score does not necessarily indicate a non-disabling stroke, and some patients with low scores may still have clinically meaningful deficits warranting intravenous thrombolysis. To reduce heterogeneity, however, enrollment was limited to patients with clinically disabling symptoms or those otherwise judged appropriate for intravenous thrombolysis, while patients with isolated mild, non-disabling deficits were excluded. Patients with planned or prior endovascular therapy were excluded to minimize confounding from mechanical reperfusion and to allow a clearer assessment of the dose–toxicity relationship of intravenous urokinase itself in this phase I setting (32, 33). Accordingly, the MTD identified in the present study should be interpreted as a foundational safety dose for patients treated without EVT, rather than as a dose directly generalizable to all patients with large-vessel occlusion. Future phase II/III studies should therefore evaluate the applicability of this dose in LVO populations separately, ideally through prespecified stratification, or, more preferably, a dedicated safety lead-in cohort in patients undergoing EVT. The study further incorporated an analysis of serum fibrinogen levels, aiming to offer an additional perspective for evaluating the risk of post-thrombolysis bleeding complications (34). By determining the MTD and characterizing the safety profile of weight-based urokinase thrombolysis, the OUTSET study will establish a scientific foundation for the next generation of clinical trials. The resulting evidence could support the development of standardized and affordable thrombolytic protocols, particularly in settings where urokinase remains a clinically relevant treatment option.

